### TiM-C Process Evaluation (WP3)

This WP will use a mixed methods design to conduct an in-depth process evaluation to explore implementation, mechanisms of action, and context [24], and investigate the impact the TiM-C system has on MND specialist center’s services. Purposive sampling will be used to recruit people with MND, their caregivers, and HCPs using TiM-C to participate in semistructured interviews, case studies, and quantitative surveys (Multimedia Appendix 1 presents an overview of when these activities will be conducted).

A process evaluation will be conducted because it is not feasible to evaluate a complex digital intervention such as TiM-C via a randomized controlled trial [10,24]. There are 5 components in this process evaluation, “local context,” “engagement,” “user experiences,” “service impact,” and “mechanisms of action”, each with its own section below and in Multimedia Appendix 1. Data collected on these components will enable an assessment of context, implementation, and mechanisms of action [24]. A triangulation protocol adapted from Farmer et al [25] will be employed to separately conduct and analyze each component before triangulating the findings.

### Description of Service and Local Context

To collect information regarding how the local context may affect the delivery and outcomes of the TiM-C service, sites will complete a survey after they begin using the system. This survey will include questions relating to what HCPs are included in the local MDT, who reviews the TiM system and how often, how issues are escalated or referred to other HCPs, and what complexities exist within the organization (informed by the complexity assessment tool of the NASSS).

Additionally, most MND MDT services conduct biannual audits. Where available, the last 2 audits will be collected to provide an overview of the level to which each site meets National Institute for Health and Care Excellence guidelines.

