**Results:**

This study has received ethical approval and has begun recruitment in 1 site. Further, 13 specialist MND centers will adopt TiM-C and the TIME study, beginning in July 2024. The study will conclude in November 2026 and a final report will be produced 3 months after the completion date.

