### Service Impact of TiM-C Upon MDT Care and the MND Service

To explore how TiM-C has affected the structure of each organization’s MDT care, the same survey completed to describe the service and local context (see “TiM-C process evaluation” section above) will be completed yearly after the first. Additionally, any audit on the MND MDT services conducted within the duration of this study will also be collected.

Semistructured interviews will be conducted with HCPs using the TiM-C system to explore their beliefs about their connectedness with users, timeliness of care, and the quality of care that they deliver. These questions will be asked at the same time as those described in 4.3.3 above, to reduce the burden the research has on participants.

To explore whether the TiM-C system has improved the experience of MND care for people with MND and their caregivers, participants will complete a patient-reported experience measure (PREM) 1 month and 12 months after they have been invited to create TiM-C accounts. Participants who have created an account will be allocated to the “user” group and those who do not create accounts will be allocated to the “non-user” group. The PREMs will be compared between these 2 groups across both data collection points. The PREM is adapted from the Client Satisfaction Scale [29].

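### The site survey meant to show how TiM-C affected MDT structure has no pre-adoption round, so it can show only early versus later post-adoption change

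*Protocol article*

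**What the plan says.** The protocol article uses one site survey for two purposes.

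- **Description.** Under Description of Service and Local Context, "sites will complete a survey after they begin using the system". It asks "what HCPs are included in the local MDT", "who reviews the TiM system and how often", how issues are escalated or referred, and what complexities exist in the organization.
- **Impact.** Under Service Impact of TiM-C Upon MDT Care and the MND Service, the same survey returns with a new aim: "To explore how TiM-C has affected the structure of each organization"'s MDT care. It "will be completed yearly after the first".

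The Description section also draws on past audits: "Where available, the last 2 audits will be collected to provide an overview of the level to which each site meets" the national guidelines. The Service Impact section adds audits carried out during the study, interviews with health care professionals (HCPs), and a patient-reported experience measure (PREM).

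On rollout, the Abstract reports recruitment open at one site and states: "Further, 13 specialist MND centers will adopt TiM-C and the TIME study, beginning in July 2024".

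**The concern.** A survey completed after TiM-C starts is suitable for describing local context, and the items about who reviews TiM-C cannot be answered any earlier. The difficulty comes when the same survey is reused to show what TiM-C changed. Its first round then becomes the reference point, and that reference is already post-adoption.

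If a site alters its MDT membership or its escalation and referral routes to accommodate TiM-C at or before the first round, the new arrangement is what the first round records. Later rounds then show no change on that item. What the repeats do capture is movement between early and later use. That is a different question from how adoption affected the structure of care, which is the aim the section states.

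**Working it through.** The plan gives no figure to reproduce here. The check is one of timing and content.

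**1. Order of events at a site.** TiM-C starts, the first survey follows (the text gives no interval), and repeats come yearly. Survey readings before the start: 0 at every site.

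**2. What the contrast contains.** For any survey item, let S0 be the state before TiM-C, S1 the state at the first survey and S2 the state at a later survey. The change since before adoption is

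S2 − S0 = (S2 − S1) + (S1 − S0).

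The planned survey observes S2 − S1 only. The term S1 − S0, which is whatever changed at or before the first round, is not observed.

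**3. Whether another source supplies S0.**

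| Source | Timing | Described as recording prior MDT membership or escalation routes? |
|---|---|---|
| Last 2 audits | May pre-date adoption; not stated to; only where available | No; described as showing guideline adherence |
| Audits during the study | Within the study period | No |
| HCP interviews | 3 and 12 months after account creation | No question on earlier practice is described |
| PREM | 1 and 12 months after invitation | No; measures patient and caregiver experience |
| Case-study observations | While TiM-C is in use, at 5 centers | No; concern how TiM-C data are used |

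No comparison sites are described and all 14 centers adopt TiM-C, so a within-site before-and-after comparison is the natural structural contrast.

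**4. Which items could be asked earlier.** MDT membership, escalation and referral routes, and organizational complexity all exist before TiM-C. Who reviews TiM-C, and how often, does not.

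**5. How many sites could still give S0.** Taking the Abstract at its word, 13 of 14 sites had still to adopt: 13/14 = 0.93. This is an upper bound, because the Introduction describes adoption as already under way across 14 centers and does not say how many were live.

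**6. Rounds available.** July 2024 to November 2026 is 24 + 4 = 28 months. If a site starts in July 2024 and is surveyed at once, rounds fall at about 0, 12 and 24 months, so at most three. A site starting after November 2024 does not reach a 24-month round before the study ends. A missed pre-adoption reading cannot be recovered prospectively later.

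**The case against.** The strongest reply has five parts.

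- **The survey is exploratory.** The section sets out to explore. It specifies no before-and-after estimate or test for the survey, and the components of WP3 are to be triangulated. This stands, and it rules out a stronger reading. A reader might infer that the result is biased toward no effect, or that later drift will be credited to TiM-C. Both describe an analysis the article does not state, and they point in opposite directions. What the text supports is narrower: the survey cannot see one part of the change.
- **Change at go-live is assumed.** A reader might infer that sites usually reorganize when TiM-C starts. The article does not say so. The economic section says TiM-C is not intended to replace any part of usual care, so an early first round could lie close to the previous structure. This also stands. The blind spot exists whatever the frequency, but its practical size is unknown.
- **Other sources inform service impact.** Audits, interviews and the PREM contribute, and staff may recount what changed. It would therefore be wrong to conclude that the whole service-impact component, or all of WP3, lacks a pre-adoption reference. Audits, where available, may even reach back before adoption on guideline adherence. None of these sources is described as recording earlier MDT membership or escalation routes, however, so they do not fill this particular gap.
- **The appendix and survey form are not shown.** Multimedia Appendix 1 may give the interval to the first round, and the form may contain retrospective items. That possibility remains open. The article itself places the first round after the start and mentions no retrospective items.
- **An earlier round is not free.** The eligibility criteria require HCP participants to belong to an MDT that has used TiM-C for at least 1 month. If the staff completing the form count as participants, a pre-go-live round conflicts with that criterion. This stands and is dealt with in the fix.

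**Conclusion.** The point holds for the site survey and its structural contrast. No survey reading pre-dates adoption at any site, so the survey shows early versus later post-adoption change and misses whatever changed at or before its first round. No other source in the plan is described as supplying the missing state.

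The size of the loss cannot be calculated, because the article gives neither how often MDT structure changes at go-live nor the interval to the first round. The opportunity to repair it is up to 13 of 14 sites (93%). A reader might take 13 as a firm count of sites not yet live, but the documents support it only as a ceiling.

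The conclusion rests on two assumptions: that the article's stated timing is what the full protocol and appendix contain, and that the survey form asks nothing about the state before TiM-C. It is an inexpensive improvement to the plan's ability to answer its own question, and not a flaw that undermines the process evaluation.

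**What to change.** 1. **Sites not yet live (up to 13 of 14).** Collect MDT membership, escalation and referral routes, and organizational complexity before go-live. Word these items so that they can be answered without TiM-C in place.
2. **All sites.** Keep the TiM-C review items after go-live, and keep the yearly repeat of the full survey.
3. **Sites already live.** Ask for the pre-TiM-C state retrospectively, and flag those answers as recalled when reporting.
4. **Reporting.** Describe survey change relative to the pre-go-live state. Where no baseline exists, word the Service Impact aim as change after adoption.

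**Cost.** The form is split into two parts, one of them moved forward, with no added burden on patients or caregivers. If the staff who complete it count as HCP participants, the criterion of at least 1 month of TiM-C use has to be waived for this site-level form. With no comparison sites, a baseline makes change around adoption visible but does not by itself attribute that change to TiM-C.

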### Engagement

Manually and automatically collected data at every site will be analyzed in accordance with an adapted version of the taxonomy of adherence Vrijens et al [26]. This will provide information relating to the uptake, initiation and discontinuation, persistence, nonpersistence, and activity of the TiM-C service.

Local HCPs will keep a record of the number of people with MND who have been invited to TiM-C and the reasons for people not creating an account if these are offered at the time of face-to-face invitation. The TiM-C system automatically collects the number of people with MND who create an account. The TiM-C system also automatically collects the number of caregivers who are invited and the number who create an account. Combining this data will provide information on uptake (the proportion of people with MND and caregivers who create an account when invited) at each site, in addition to reasons for nonuptake that can be used to develop the invitation process.

If available at the MND center, demographics and routinely collected data will be analyzed to investigate whether there are any statistically significant differences between those who do and do not create TiM-C accounts. Relevant data may include, age, gender, partial postcode (to explore the effects of deprivation), and outcomes relevant to MND such as functional rating, date of onset, site of onset, and date of diagnosis. Statistical analyses will include *t* tests and chi-square tests for parametric and nonparametric data, respectively.

The TiM-C system automatically collects anonymized data relating to the date and time people with MND and caregivers complete a questionnaire. This data will be analyzed to calculate initiation and discontinuation (the date of first and last questionnaire completion, respectively), persistence (the time from first to last questionnaire completion), nonpersistence (the time following persistence during which no questionnaires are completed), and activity (the percentage of questionnaires completed during persistence). Similar to the above, if data is available, statistical analyses will be conducted to investigate whether any aspect of engagement can be predicted by individuals’ demographics or disease-relevant data.

TiM-C also automatically collects the number of times an HCP logs into the system and sends feedback or resources to people with MND and caregivers. These data will be aggregated to calculate how often the TiM-C system is reviewed and used to send information to people with MND and caregivers.

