**Methods:**

WP1 will use semistructured interviews with 10-15 people involved in the approval of TiM-C to understand the barriers and facilitators to governance processes. WP2 will use individual and group interviews with 25-35 users (people with motor neuron disease, caregivers, HCPs, MND researchers, and industry) of TiM-C and TiM-R to understand the current unmet needs of these user groups and how TiM services can be developed to meet these needs. WP3 will use a process evaluation involving 5 elements; local context, engagement, user experiences, service impact, and mechanisms of action. A range of methods, including audits, analysis of routine data, questionnaires, interviews, and observations will be used with people with motor neuron disease, caregivers, and HCPs, both those using the system and those who declined the service when invited. WP4 will use data collected through the process evaluation and known costs to conduct a cost-consequence and budget impact analysis to explore the cost-benefit of the TiM-C service. Most data collected will be qualitative, with thematic and framework analysis used to develop themes from transcripts and observations. Descriptive statistics or *t* tests and chi-square tests will be used to describe and analyze quantitative data.

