## Methods

### Design

The design of this project was based upon multiple frameworks and guidelines, which have helped develop a logic model, consider outcomes, and data collection methods. These include the MRC framework for the development and evaluation of complex interventions [14], National Institute for Health and Care Excellence Evidence Standards Framework [15], Person-based approach to intervention development [13], and Non-adoption, Abandonment, Scale-up, Spread, and Sustainability (NASSS) [16]. A total of 14 sites will collect data, however, some work packages (WPs) will only use a subset of sites (eg, WP1 only collects data from 5). The project has 4, interconnected WPs, which answer the research questions above:

Governance approval strategy development (research question 1)TiM-C and TiM-R codevelopment (research questions 2 and 3)TiM-C process evaluation (research question 4)TiM-C economic evaluation (research question 5)

Through the NASSS framework and the collection of other data in the 2nd and 3rd work packages (described below), we will collect information that can be used to identify barriers that affect TiM-C and TiM-R implementation and use. Throughout the study, using an implementation science lens, we will address identified barriers to facilitate the uptake of the TiM system, using methods suggested by Cane et al [17]. We will document any adaptations made to our governance approval strategy or the TiM intervention.

To reduce the number of under-served groups within this project, the research team will aim to involve a diverse range of participants throughout the entirety of this study and overcome known barriers to participation [18]. This will include remote research activities to reduce the need to travel, support for caregivers to enable participation, and continual data monitoring to ensure representative inclusion of different ages and genders.

Each of the 14 sites involved in this study will be given permission to mildly modify research activities to enable people with different abilities or circumstances, who meet the eligibility criteria, to participate in any and all parts of the study they want to. For example, modifying consent or data collection procedures to enable the participation of people with MND and caregivers who are physically unable to complete documents, or questions being shared ahead of an interview to allow participants who have difficulty communicating time to prepare recorded answers.

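### The Engagement section misstates its test rule: chi-square is for categorical variables and does not replace the t test when data are skewed or ordinal

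*Protocol article*

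**What the plan says.** The Engagement section (WP3) plans, where routine data are available, to look for "statistically significant differences between those who do and do not create TiM-C accounts". The candidate variables are age, gender, partial postcode as a route to deprivation, and disease measures: "functional rating, date of onset, site of onset, and date of diagnosis". The analyses are to include *t* "tests and chi-square tests for parametric and nonparametric data, respectively".

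The same section then plans to "investigate whether any aspect of engagement can be predicted by" demographic and disease data. It describes this as similar to the preceding analysis and names no method.

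The Methods part of the abstract covers all quantitative work in one clause: descriptive statistics, or *t* "tests and chi-square tests will be used to describe and analyze quantitative data". No other inferential method is named anywhere in the article.

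The Service Impact section says that "participants will complete a patient-reported experience measure (PREM) 1 month and 12 months after they have been invited". It compares users with non-users over both time points and names no test.

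**The concern.** A *t* test compares means of a continuous variable. A chi-square test compares distributions over categories. Which one applies depends on what kind of variable is being compared. Calling data parametric or nonparametric does not settle it. When a continuous variable is too skewed for a *t* test, or a score is ordinal, the usual alternative is a rank-based test or a transformation.

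This is a rule that the article states, not a detail left to another document. An analyst who follows it would group skewed or ordinal variables at chosen cut-points and so discard information. The cut-points would add an arbitrary choice. At stake is the description of who takes up TiM-C and who does not, which the article wants in order to understand engagement and non-engagement.

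**Working it through.** **Step 1. Apply the rule to the listed variables.** The article gives no sample size, SD or effect size for this comparison, so there is no figure of its own to reproduce. The types below follow from what each variable is. Turning dates into durations is an assumption, since the article does not say how dates will be used.

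| Variable | Type | Rule as written | Test that fits the type |
|---|---|---|---|
| Age | continuous | *t* test if judged parametric, otherwise chi-square after grouping | Welch *t* test, or Mann-Whitney if skewed |
| Gender | categorical | no clear place | chi-square or Fisher exact |
| Partial postcode (deprivation) | ordinal or categorical | unclear | Mann-Whitney if ranked, chi-square if unordered |
| Functional rating | ordinal score | chi-square after grouping, if judged nonparametric | Mann-Whitney |
| Time since onset, time since diagnosis | continuous, probably skewed | chi-square after grouping | Mann-Whitney |
| Site of onset | categorical | no clear place | chi-square or Fisher exact |

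Skewed durations are a realistic expectation here. The Introduction gives an average life expectancy of 2 to 3 years after diagnosis, with a course running from a few months to more than 10 years.

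**Step 2. Illustrate the cost on assumed data.** Assumptions: two groups of 100; a lognormal variable with log-scale SD 1; a log-scale difference of 0.4; two-sided 5% level; 4,000 simulated data sets.

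| Test | Power |
|---|---|
| Mann-Whitney | 0.78 |
| Chi-square on a median split | 0.66 |
| *t* test on the untransformed values | 0.60 |

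The simulation error is small: √(0.66 × 0.34 / 4000) = 0.0075 for the middle row. As a plausibility check, a *t* test on the log values has noncentrality 0.4 / √(1/100 + 1/100) = 2.83, so its power is about Φ(2.83 − 1.96) = Φ(0.87) = 0.81. Mann-Whitney comes close to that.

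The loss against Mann-Whitney is 0.78 − 0.66 = 0.12 if the rule is followed literally. It is 0.78 − 0.60 = 0.18 if the skewed variable goes to the *t* test instead. These figures belong to this one assumed scenario. They show the direction of the loss. Its size in this study would depend on the actual skewness, group sizes and differences.

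**Step 3. Set the abstract beside the other planned analyses.**
- The PREM comparison has two groups and two time points. A two-sample test can compare groups at one time point, or compare one change score per person. It cannot use both measurements of each person jointly as separate records without an assumption of independence.
- Persistence is a duration and activity is a percentage. Relating either to age or functional rating by *t* or chi-square tests would require grouping one side, and these tests cannot adjust for other predictors.
- "A total of 14 sites will collect data", and uptake is defined as "the proportion of people with MND and caregivers who create an account when invited". Site and patient-caregiver pairing are therefore part of the data structure, and the article does not describe how either will be modelled.

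Step 3 supports a question to the authors. It does not show an error, because the sections concerned name no test.

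**The case against.** The most natural defence is that nonparametric is loose wording for categorical. Gender and site of onset are on the list, so the authors may have meant *t* tests for continuous variables and chi-square for categorical ones. That reading is plausible and makes the error smaller, but the sentence would still need correcting. It would also leave skewed and ordinal variables with the *t* test alone, which did worst in the illustration.

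It is also fair to say that the comparison is exploratory and depends on available data. It sits in a process evaluation whose data are mostly qualitative, and no primary hypothesis or sample size rests on it. This stands, and it limits the weight of the point.

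A reader might go further and infer that the study's p-values will be wrong because site, patient-caregiver pairs and repeated PREMs are ignored. The article does not support that:
- The test rule is attached to the account-creation comparison only. It says what the analyses will include, which does not exclude other methods.
- No section says that pairs or visits will be pooled, or that site will be left out. A condensed article commonly leaves such modelling to the full protocol or SAP.
- Even the direction of any error is unknown. Assume a correlation of 0.3 to 0.7 between two records. Pooling both in the same group as independent gives a true error of 2[1 − Φ(1.96/√(1+ρ))], which is 0.086 to 0.133 at a nominal 0.05. Testing a within-person change as unpaired gives 2[1 − Φ(1.96/√(1−ρ))], which is 0.019 down to 0.0003.
- Ignoring site leaves the error at about 0.05 if uptake is the same across sites. In simulations with 14 sites, an assumed 40 people per site and intraclass correlations of 0.02 to 0.10, it rose to between 0.06 and 0.12 only when uptake varied between sites (logit SD 0.5 to 1.0).

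A reader might also apply the textbook efficiency of 2/π for median-splitting a normal variable. The stated rule sends normal variables to the *t* test, so that figure describes a case that the rule excludes.

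**Conclusion.** The test rule in the Engagement section is wrong as stated and should be corrected. It assigns tests by a parametric or nonparametric label where variable type should decide, and it names no test suited to skewed continuous or ordinal variables. The consequence is avoidable loss of power and arbitrary grouping in the comparison of account creators with non-creators. In one assumed scenario, power was 0.66 (literal reading) or 0.60 (charitable reading) against 0.78 for a rank-based test. The conclusion that the rule is misstated needs no assumption; the size of the loss rests entirely on the assumed distribution, difference and group sizes.

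This is a modest correction to a secondary, exploratory analysis. How the PREM comparison and the engagement prediction will be modelled is an open question for the authors and is not an established fault.

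**What to change.** Replace the sentence in the Engagement section with a rule by variable type:
- chi-square test, or Fisher exact test where counts are small, for categorical variables such as gender and site of onset;
- Welch *t* test for approximately normal continuous variables;
- Mann-Whitney test for skewed or ordinal variables such as functional rating and time since onset or diagnosis.

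State that dates will be analysed as durations, if that is intended, and bring the Methods part of the abstract into line.

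As a query, ask the authors to confirm that engagement prediction will use regression, and that the PREM comparison will use a regression or mixed model accounting for the two time points, site and any patient-caregiver pairing. If the full protocol or SAP already says so, a short reference to it is enough.

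The cost is a few sentences and standard software. No design feature, data collection or sample size changes. The abstract reports recruitment begun at one site, so the wording can be settled before most data exist.
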